### Economical evaluation

An economic evaluation will be performed after 24 months from the societal perspective and from the health insurance perspective. Differences in mean costs between the two groups will be presented with 95% confidence intervals, estimated with bootstrapping methods. Incremental cost-effectiveness ratios (ICERs) will be calculated by dividing the incremental mean costs by the incremental mean effects for: a) reduction in the risk of developing diabetes based on the ARIC score, b) reduction in the risk of future cardiovascular disease based on the SCORE, and c) quality-adjusted life years (QALYs) based on the EuroQol. The 'Dutch EQ-5D tariff' [48] will be used to calculate utilities.

Bootstrapping methods will be used to derive cost-effectiveness planes and acceptability curves.

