### Study population

Twelve thousand inhabitants (men and women) aged 30-50 living in this region will be invited to participate in a selective screening procedure. The target group will be approached, after identification of date of birth and absence of diabetes or known CVD, from participating general practices (n = 12).

In the first step of the screening procedure the inhabitants will receive an invitation to measure their own waist circumference with a tape measure, according to detailed instructions. Waist circumference is a widely used indicator of abdominal obesity in population studies. To minimize non-response we will use the modified Tailored Design Method [32] to approach potential participants. The main elements of this approach are: a brief pre-notice postcard is sent to each of the sampled persons, and a few days later a comprehensive and easy to understand invitation is sent, together with the tape measure and a stamped addressed envelope for the reply. A week after this mailing, another postcard will be sent, in which the respondents are thanked for returning the survey questions and the non-respondents are asked to complete the waist-measurement and return it immediately. Four weeks later, a reminder and a replacement tape measure are sent to the non-respondents. Abdominal obesity is, in principle, defined as a waist circumference of 88 cm or more for women, and 102 cm or more for men [33]. All respondents with a waist circumference of 1 cm under this cut-off point or above will be invited to participate in the second step of the screening at the research center. After signing an informed consent form, this screening will include the measurement of blood pressure, a blood sample (to determine total and HDL cholesterol, triglycerides, fasting plasma glucose, HbA1c), and anthropometric measurements (height, weight, and waist and hip circumference). In addition, the participants will be given a questionnaire to fill in at home, including questionnaires about physical activity, dietary intake, smoking status, determinants of behavior according to the TPB, quality of life, and depression.

The 9-year risk of developing diabetes will be estimated using the risk function derived from data of the Atherosclerosis Risk In Communities (ARIC) Study [34], with ethnicity (black yes/no), parental history of diabetes, systolic blood pressure, waist circumference and height (Additional file 1).

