### Study duration

The counseling sessions will last for 2-4 months, and the total intervention period, including booster calls, will be 16 months. Together with an estimated inclusion period of 8 months, the study itself will take 24 months (2 years). The measurements will be carried out before the start of the intervention, and after 6, 12 and 24 months. The baseline measurements started on February 14^th^, 2008.

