### Data-collection

#### Questionnaires

▪ Dietary behavior: An extended and modified version of the 8-item Food Frequency Questionnaire [39] will be used to measure the intake of fruit, vegetable, fiber, alcohol consumption and (un)saturated fat. Total energy intake can not be measured with this questionnaire.

▪ Physical activity behavior: The Short Questionnaire to Assess Health Enhancing Physical Activity (SQUASH) [40] will be used to assess physical activity within (A) commuting activities, (B) leisure time activities, (C) household activities, and (D) activities at work and school.

▪ Sedentary behavior during leisure time will be measured with a subscale of the Activity Questionnaire for Adolescents & Adults (AQUA) [41].

▪ Smoking behavior: Smoking every day/smoking now and then/never smoked/year of smoking cessation and pack years (average number packs of 20 cigarettes per day smoked, multiplied by the number of years as a smoker).

▪ Determinants of behavioral change: A 41-item questionnaire, based on existing TPB questionnaires, will be used to assess lifestyle-specific behavior with regard to the constructs attitude, social norm, self-efficacy and intention to change. To our knowledge, no suitable validated questionnaires are available. The theoretical model and questionnaires in other current studies at the research institute were used to develop this Determinants of Lifestyle Behavior Questionnaire (DLBQ).

▪ Quality of life will be assessed with the EuroQol (EQ-5D) [42,42,43].

▪ Compliance: The number of CBP sessions attended will be registered, and compliance is considered adequate if at least two sessions are attended.

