### Analyses

Descriptive statistics (means ± SD, or median and interquartile ranges, as appropriate) will be used to describe the entire study sample with regard to demographics, physical measurements and baseline lab values. The analyses will be conducted according to the intention to treat principle. Multilevel analyses will be performed to adjust for the clustering of observations of participants receiving care from the same nurse practitioner, and for repeated measurements within one patient. Linear and logistic regression models will be used to examine the effect of the intervention on each of the outcome measurements. Differences in changes between groups will be calculated with 95% confidence intervals. If there are any relevant differences in baseline measurements between the two groups, we will adjust the outcome for these factors (i.e. age, gender, ethnicity, BMI at the start of study, level of education, depression, smoking, number of sessions attended). Separate analyses of effect modifiers (i.e. gender, age) will be performed in order to gain a better understanding as to who benefits most from the intervention. Separate analyses of effect modifiers and mediators will be conducted in order to gain a better understanding as to who benefits most from the intervention

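### The cost-utility analysis names no adjustment of the QALY difference for baseline EQ-5D, so it forgoes precision that data already collected would give at almost no cost

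*Protocol article*

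**What the plan says.** All references are to the Protocol article.

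- **Economical evaluation** defines the ratios: "Incremental cost-effectiveness ratios (ICERs) will be calculated by dividing the incremental mean costs by the incremental mean effects for" three effects. The first two are reductions in ARIC and SCORE risk. The third is "quality-adjusted life years (QALYs) based on the EuroQol".
- For costs, the same section states: "Differences in mean costs between the two groups will be presented with 95% confidence intervals, estimated with bootstrapping methods". Bootstrapping also produces the cost-effectiveness planes and acceptability curves. No covariate is named for costs or effects.
- **Study population** shows that the questionnaire at the second screening step covers "determinants of behavior according to the TPB, quality of life, and depression". **Questionnaires** names the EQ-5D as the quality-of-life instrument. **Study duration** gives the schedule: "The measurements will be carried out before the start of the intervention, and after 6, 12 and 24 months".
- **Analyses** states: "Linear and logistic regression models will be used to examine the effect of the intervention on each of the outcome measurements". It reports between-group differences in change and adds: "If there are any relevant differences in baseline measurements between the two groups, we will adjust the outcome for these factors". The factors then listed are demographic characteristics, BMI, education, depression, smoking and session attendance. EQ-5D is not among them.

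**The concern.** The first two effects are worded as reductions, which suggests a change from baseline. The QALY effect is not. It is normally the area under the utility curve over 24 months, and baseline utility affects that area in two ways: it is the first point of the curve, and it predicts every later point. If one arm starts with slightly higher utility by chance, the unadjusted QALY difference inherits that advantage.

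The rule in Analyses does not clearly close this gap. It depends on someone judging a difference relevant, and its list omits EQ-5D. It also sits beside a description of differences in change, which a QALY is not. At 300 per arm, one standard error of a baseline difference is sqrt(2/300) = 0.08 SD, whatever the SD is. An imbalance of that size would hardly be called relevant, yet it still moves the QALY difference.

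At stake is the width of the uncertainty around the cost-utility result. Any QALY gain over two years in people aged 30 to 50 is plausibly small, so precision matters.

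**Working it through.** **No figure to reproduce.** The article gives no EQ-5D standard deviation, between-visit correlation or expected QALY gain. Its only inputs here are the visit times (Study duration) and 300 per arm (Sample size). The rest is assumed and shown as a range.

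**Step 1: weights.** A trapezium over 0, 0.5, 1 and 2 years gives weights 0.25, 0.50, 0.75 and 0.50, summing to 2.0. The article states no QALY formula, so this is an assumption.

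**Step 2: formulae.** Assume the same SD s at each visit and the same correlation r between any two visits.

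- Sum of squared weights: 0.0625 + 0.25 + 0.5625 + 0.25 = 1.125. Cross terms: 2.0² − 1.125 = 2.875. So Var(QALY) = s²(1.125 + 2.875r).
- Covariance of the QALY with baseline utility: s²(0.25 + 1.75r). The bracket is also the expected shift in the unadjusted QALY difference per unit of baseline imbalance.
- Share of variance removed by baseline adjustment: (0.25 + 1.75r)² / (1.125 + 2.875r). Its square root is the shift from a one-standard-error imbalance, in units of the unadjusted standard error.

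**Step 3: results.**

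| Assumed r | 0.25 + 1.75r | 1.125 + 2.875r | Variance removed | Shift from a one-SE imbalance, in SEs of the QALY difference |
|---|---|---|---|---|
| 0.2 | 0.600 | 1.7000 | 21% | 0.46 |
| 0.3 | 0.775 | 1.9875 | 30% | 0.55 |
| 0.5 | 1.125 | 2.5625 | 49% | 0.70 |
| 0.7 | 1.475 | 3.1375 | 69% | 0.83 |
| 0.8 | 1.650 | 3.4250 | 79% | 0.89 |

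**Step 4: sensitivity.** If correlation decays with time, at 0.3 to 0.8 per year, the share removed is 30% to 76%. If baseline is left out of the area (weights 0, 0.50, 0.75, 0.50), it is 17%, 37% and 61% at r = 0.3, 0.5 and 0.7.

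**Step 5: on the QALY scale.** Take an assumed s = 0.20, r = 0.5 and 300 per arm.

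- SE of the baseline difference: 0.20 × sqrt(2/300) = 0.016.
- Shift from a one-SE imbalance: 1.125 × 0.0163 = 0.018 QALY.
- Unadjusted SE of the QALY difference: 0.0163 × sqrt(2.5625) = 0.026.
- Adjusted SE: 0.0261 × sqrt(1 − 0.494) = 0.019.

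These scale in proportion to s. For s from 0.10 to 0.25, the unadjusted SE runs from 0.013 to 0.033 and the adjusted SE from 0.009 to 0.023. The percentages in Step 3 do not depend on s.

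**The case against.** The strongest reply is that the article never says the means are unadjusted. It gives the standard definition of an ICER, and a regression-adjusted mean difference fits that wording. Analyses promises regression for each outcome measurement, and cost-utility is listed among the secondary outcomes, so the conditional rule may be meant to reach it. A condensed article may also leave the model to a fuller plan. This stands to the extent that an unadjusted analysis is an inference from the text. It does not remove the point: the estimator and the adjustment factors are both described, and neither mentions baseline utility.

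A reader might draw four stronger conclusions. The documents do not support them.

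- **That the QALY comparison is biased, or its sign decided by baseline chance.** Randomization makes the unadjusted difference unbiased. A one-SE imbalance moves it by about 0.7 to 0.8 of its own SE at r = 0.5 to 0.7, which is ordinary sampling variation. The planned bootstrap will display that uncertainty, although it will not reduce it.
- **That all three ICERs are affected, with two conflicting effects reported for ARIC and SCORE.** Those effects are worded as reductions, and nothing says they will differ from the estimates in Analyses.
- **That baseline EQ-5D is thrown away.** It would normally form the first point of the area. What is missing is its use as a covariate.
- **That the shift, valued in money, rivals the cost of the program.** The article gives neither a value per QALY nor a program cost. Its societal perspective also counts hospitalization, medication and lost work, so session costs alone are not the incremental cost.

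**Conclusion.** The point holds as a precision improvement limited to the QALY ratio. As written, the article provides no adjustment of the QALY difference for baseline EQ-5D, although that measure is collected. The unadjusted difference is valid but wider than necessary.

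The gain is about 30% to 69% of the variance for assumed correlations of 0.3 to 0.7, and 21% to 79% for 0.2 to 0.8. These figures rest on a four-point trapezium, equal SDs, equal correlations, complete data and no clustering. None of the EQ-5D inputs comes from the article, and the correlation in this population is unknown, so the lower end is possible. The direction does not depend on the exact value: any appreciable correlation between baseline and later utility gives a gain.

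**What to change.** In Economical evaluation, state that:

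1. incremental QALYs are estimated by regression on treatment arm and baseline EQ-5D utility, whatever baseline imbalance is observed;
2. this regression is bootstrapped jointly with the cost comparison, resampling the same participants so that the correlation between costs and effects is kept;
3. the cost-utility ratio, its cost-effectiveness plane and its acceptability curve are built from the adjusted QALY difference.

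If a fuller plan already does this, one clause in the article saying so is enough. The cost is a change of wording and slightly more analysis work. No new data, visits or participants are needed.

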## Discussion

This article presents a detailed description of an RCT, designed with the aim to investigate the effectiveness of a CBP to improve lifestyle behavior and reduce T2DM and CVD risk in a high-risk population. This will provide researchers, health care providers and policy makers the opportunity to critically review the methodological quality, the background theory and the practical issues of the RCT. An innovative and key element of this trial is that the participants will be self-empowered to accomplish a long-lasting change in their lifestyle. We expect that the specific counseling methods (MI and PST) will induce an effective, sustained reduction in T2DM and CVD risk. Both counseling methods are practical, evidence-based tools. The combination of MI and PST, in particular, is used before [49], but never in preventive trials. Combining the two counseling methods may be effective because PST can help to resolve the ambivalence created with MI. By doing so, practical tools to sustained pro-active behavioral change are handed to the participants, who become aware of their unhealthy behavior and are intrinsically motivated to change. The participants will be free to choose which lifestyle component(s) (smoking, physical activity or diet) they want to change. Offering different behavioral alternatives to achieve the participant's goals may positively affect compliance and long-term success.

After the counseling the participants will receive continuing support in the form of 3-monthly booster sessions by phone, which will help them to sustain behavioral changes.

There are some limitations in the study design. Critics may raise concerns about the use of the DLBQ to assess determinants of change in lifestyle behavior, because this questionnaire has not been validated. We developed this questionnaire by using several questionnaires of colleagues in the field since we were not able to find a validated questionnaire to assess determinants of behavior. Another concern could be the benefit participants in the intervention group may have from the extra attention they get. However, attention alone is unlikely to result in behavioral change. Furthermore, it has been demonstrated that MI and PST are significantly more effective than attention alone [50-52].

Non-respondents are a potential threat to the external validity of a study. Therefore we chose to approach potential participants with correspondence at multiple moments, as described by Dillman et. al. [32]. The intervention will take place in close proximity to the homes of the participant, and this could reduce barriers for participation. Furthermore, two bicycles will be raffled among those who respond to the first screening step. Despite of these measures, we expect that participants who agree to participate are higher educated and more willing to change their lifestyle than the non-respondents [53]. However, because the participants will be randomized, this will be the case in both groups. Having a population of motivated participants might decrease the drop-out percentage.

A strength of the study design is its focus on lifestyle dependent risk factors that are associated with both T2DM and CVD. To select people who are at risk of these diseases, self-measured waist circumference is used as a first screening step, which is a simple and practical method. Another strength is the careful monitoring of the intervention by providing standardized training for the nurse practitioners and feedback on the counseling sessions by means of tape recordings.

If this intervention has strong positive effects, the CBP could be widely implemented. The process evaluation of our intervention will come up with barriers and facilitators that can be used for the implementation strategy.

## Abbreviations

ARIC: atherosclerosis risk in communities; AQUA: activity questionnaire for adolescents & adults; BMI: body mass index; CBP: cognitive behavioral program; CVD: cardiovascular diseases; DLBQ: determinants of lifestyle behavior questionnaire; GP: general practitioner; ICERs: incremental cost-effectiveness ratios; MI: motivational interviewing; MITI: motivational interviewing treatment integrity; PST: problem solving treatment; RCT: randomized controlled trial; T2DM: diabetes mellitus type 2; TPB: theory of planned behavior; QUALYs: quality adjusted life years; SQUASH: short questionnaire to assess health enhancing physical activity.
